## Abstract

**Background:**

Effective control of postprandial glucose responses (PPGRs) is essential for managing the progression of type 2 diabetes mellitus (T2DM). Carbohydrate-rich staple foods are known to induce significant variability in PPGR among individuals.

**Objectives:**

This study aimed to investigate the personalized PPGR to various staple foods among patients with diabetes using an *N*-of-1 trial design.

**Methods:**

A single-center, randomized, crossover *N*-of-1 trial is planned. Participants will receive 5 different staple foods (white rice, germ rice, brown rice, rice noodles, and pasta) 3 times in a randomized order. Continuous glucose monitoring will track PPGR at 5-min intervals. The primary outcome will be the postprandial blood glucose peak. The Bayesian analysis will be conducted at both individual and group levels to access the PPGR for staple foods.

**Discussion:**

By using the *N*-of-1 trial methodology, this study is anticipated to reveal substantial interindividual variations in PPGR and to identify staple foods that are most effective in stabilizing blood glucose concentrations for individual patients, providing insights into personalized nutritional management for T2DM.

This trial was registered at Chinese Clinical Trial Register as ChiCTR2400090138 (24 September, 2024).

## Introduction

According to the International Diabetes Federation, in 2021, ∼540 million individuals aged 20–74 y were living with diabetes worldwide, and this number is expected to rise to 640 million by 2030 [1,2]. Consequently, diabetes constitutes a substantial disease burden and economic loss globally, underscoring its prevention and management as a critical international public health priority.

Postprandial hyperglycemia has been identified as a key factor in the aggravation and progression of diabetes [3]. Dietary components, particularly the quality and type of staple foods, are significant determinants of blood glucose concentrations and thus play an extremely critical role in the development and management of type 2 diabetes mellitus (T2DM) [4]. Staple foods, which are the primary sources of carbohydrates and energy in the diet, directly impact blood glucose concentrations. Typical staple foods include grains (e.g., rice and wheat) and tubers (e.g., potatoes), with rice constituting ∼70% of the daily caloric intake in developing countries in Asia [5]. The glycemic index (GI) is a metric that quantifies the impact of dietary carbohydrates on blood glucose concentrations, indicating the rate and extent of their digestion, absorption, and subsequent entry into the bloodstream. Recent research has identified several staple foods with a lower GI or other characteristics that can attenuate postprandial glucose responses (PPGRs), including pea noodles and oat noodles [6,7]. It is important to acknowledge that these findings pertain to the intrinsic properties of the foods consumed.

However, glycemic responses to identical foods exhibit substantial interindividual heterogeneity, with significant intraindividual variations even across different contexts [8]. It is noteworthy that such variations exist equally in both diabetic and nondiabetic individuals, which undermines the practical utility of standardized dietary guidelines [9]. Sayegh et al. [10] found that among subjects consuming the same test meal, the variability in PPGR ranged from 25% to 56% both between individuals and within the same individual. This variability may originate from 3 interrelated domains: biological characteristics, food properties, and behavioral contexts. Physiologically, insulin resistance delays the clearance of glucose, whereas the composition of the gut microbiota regulates the rate of carbohydrate fermentation and the efficiency of glucose absorption [11]. Studies have shown that the abundance of *Prevotella copri* is negatively correlated with the SD of blood glucose concentrations [12]. Genetic variations in glucose transporters (e.g., *SLC2A2*) further contribute to different metabolic responses [13]. Refined grains, which lack the fiber that slows digestion, and cooking methods (e.g., overcooking rice) alter the starch structure, increasing their glycemic potential [14]. Meanwhile, behavioral factors such as eating quickly or chronic stress exacerbate blood glucose fluctuations by disrupting satiety signals and insulin sensitivity [15]. These findings highlight the limitations of using average group GI values to predict individual glycemic responses. Consequently, for patients with diabetes, the selection of staple foods that align with individual needs is essential for managing PPGR. Personalized nutrition, which emphasizes the importance of customization based on individual differences, involves tailored dietary recommendations and nutritional plans that consider specific needs, physiological characteristics, genetic backgrounds, health conditions, and lifestyles [16,17].

Single-case randomized controlled trials, also known as *N*-of-1 trials, provide novel insights into personalized nutrition research [18]. These trials determine individual responses to specific interventions through prospective, randomized crossover designs conducted either on individual patients or a series of patients [19]. Previous studies have used *N*-of-1 trials to explore individual differences in PPGR to diets with varying macronutrient compositions in healthy adults [20]. However, the personalized differences in PPGR to various staple foods among patients with diabetes remain understudied.

The present study uses *N*-of-1 trials to investigate the personalized differences in PPGR to different staple foods in patients with diabetes, thereby providing new insights and evidence for personalized nutritional interventions in diabetes management.

## Methods

### Study design

A randomized, 3-period crossover *N*-of-1 trial will be conducted to assess the individual variation in the consumption of staple foods.

### Setting

The study will be conducted at the Institute of Biotechnology and Health, Beijing Academy of Science and Technology in Beijing. The study has obtained ethical approval from the Inner Mongolia Nutrition Society Ethics Committee (NO.A202309002) and is registered with the Chinese Clinical Trial Register (ChiCTR2400090138).

### Study population

Participants will be recruited from communities through advertisements posted on community bulletin boards in Beijing. The inclusion criteria of the participants are as follows: *1*) age between 18 and 70 y; *2*) T2DM diagnosis by an endocrinologist for ≥3 mo; *3*) currently under lifestyle intervention alone or stable single hypoglycemic drug treatment; *4*) be able to operate a smartphone; and *5*) be able to provide written informed consent. The exclusion criteria include the following: *1*) pregnancy, breastfeeding, or plans to become pregnant; *2*) severe metabolic disorders, gastrointestinal diseases, or psychiatric conditions; *3*) use of antibiotics within the past month prior to enrollment; *4*) adherence to special dietary patterns (e.g., ketogenic diet and low-carbohydrate diet); *5*) difficulty with chewing foods; *6*) a history of allergies or intolerance to the test foods; and *7*) frequent travelers.

Participants will maintain daily medication logs, and the research team will verify adherence through telephone follow-ups. Any adjustments to medication during the trial will result in the participant’s exclusion. If the person is interested in the study, the study investigator will schedule a personal online or a face-to-face meeting to provide oral information and answer questions. Prospective participants will be informed that they have ≥24 h to consider their participation in the study. Should they choose to participate, both the participant and the study investigator will sign the written informed consent, after which the investigator will conduct the screening process. If all inclusion criteria are fulfilled, and none of the exclusion criteria are met, the person will be included in the study. Participants have the right to withdraw from the *N*-of-1 trial at any time. All instances of participant dropout or trial interruption will be documented, including the time and reason for discontinuation.

### Informed consent statement

Informed consent was obtained from all participants and/or their legal guardians before participating in this study. This study will be conducted in accordance with the Declaration of Helsinki.

### Test diets

The staple foods were cooked, and the main nutritional compositions of cooked (ready-to-eat) staple foods were analyzed by the Beijing Institute of Nutritional Resources, with the results presented in Table 1. To enhance the participants’ dining experience and contextualize the staple food within a typical breakfast setting, 5 test diets will be designed: white rice, germ rice, brown rice, rice noodles, and pasta. The variable component of the test diet is staple food; all other elements remain consistent. Each test diet includes a staple food providing 50 g of available carbohydrates, alongside 150 g of scrambled eggs with tomatoes, 50 g of cucumber, and 200 mL of milk. The detailed menus of each test diet can be found in Table 2.

**TABLE 1 tbl1:** Nutritional composition of 5 test staple foods in the *N*-of-1 trials (g/100 g)^1^.

Test subject	Protein	Fat	Total carbohydrates	Total dietary fiber	Available carbohydrates
Refined rice	2.80	0.2	35.4	0.378	35.0
Brown rice	2.89	1.0	31.7	2.830	28.9
Germ rice	2.38	0.5	29.1	0.474	28.6
Rice noodles	5.24	0.5	28.6	3.35	25.3
Pasta	3.69	0.4	29.6	1.540	28.1

1 The values were determined based on the cooked state (ready-to-eat).

**TABLE 2 tbl2:** A sample staple menu of the first cycle (period 1) of the *N*-of-1 trial^1^.

Food items	Test diet A	Test diet B	Test diet C	Test diet D	Test diet E
Refined rice (g)	143.0	—	—	—	—
Brown rice (g)	—	173.0	—	—	—
Germ rice (g)	—	—	175.0	—	—
Rice noodles (g)	—	—	—	198.0	—
Pasta (g)	—	—	—	—	178.0
Stir-fried tomato and eggs (g)	150.0	150.0	150.0	150.0	150.0
Cucumber (g)	50.0	50.0	50.0	50.0	50.0
Milk (mL)	200.0	200.0	200.0	200.0	200.0

1 Each subject was assigned a randomized staple food menu across the 3 cycles (sets) of the *N*-of-1 trials. The available carbohydrate content for each staple food was standardized to 50 g, and the weights of the staple foods for the 6 interventions were prepared accordingly. Each staple food intervention included the same weight of side dishes (scrambled eggs with tomatoes, cucumber) and milk to ensure balanced dietary intake.

### Study procedures

The study scheme is outlined in Figure 1. The study consists of 3 periods, each of which comprised 5 test days. On each test day, a different test diet will be consumed for breakfast. Within each period, the 5 test diets will be administered in a randomized sequence. By referring to the washout period duration (48 h) in previous studies by Zavitsanou et al. [21] and considering that key indicators such as postprandial blood glucose-related parameters can return to baseline concentrations within 2–3 d (thus effectively eliminating the residual effects of the dietary used in the previous test), a 3-d washout period was set between each test in this study. During the washout period, subjects were instructed to maintain their regular dietary habits [21,22]. To ensure consistency across test diets and to minimize the impact of prior dietary intake, participants will be advised to restrict their consumption of high-protein, high-fat, and high-fiber foods on the day preceding the test day. Additionally, they will be provided with a balanced dinner on the evening before the test day and will be required to fast for 12 h prior to the test diet. They will also be instructed to avoid strenuous physical activity and alcohol consumption on the day before the test day, with this requirement reinforced through both in-person and WeChat-based instructions. Except for the differences in the random allocation sequence of the 5 test diets, the other study procedures across the 3 periods are identical, such as blood glucose monitoring, safety evaluation, duration of the washout period, and provision of balanced dinners.

**FIGURE 1 fig1:**

Flowchart of *N*-of-1 trials for personalized differences in staple foods with diabetes. (Except that the 5 test diets are administered in an independently generated randomized sequence within each period, the other study procedures across the 3 periods, such as continuous glucose monitoring, safety evaluation, duration of the washout period, and provision of balanced dinners, are identical.) CGM, continuous glucose monitoring.

On the test day, participants will be required to rest for ≥10 min prior to the serving of the test diet. The test meal will be prepared and served at the Beijing Institute of Nutritional Resources restaurant across all participants. The cooking of each staple food follows strictly standardized preset procedures, using a fixed staple-to-water ratio and cooking time. For white rice, brown rice, and germ rice, the ratio of staple food (grams) to water (milliliters) is 1:1.25, and they will be cooked for 40 min using a Supor SY-60YC8001Q rice cooker (Zhejiang Supor Co, Ltd.). For rice noodles and pasta, the mass-to-volume ratio of staple food (grams) to water (milliliters) will be set to 1:10 to ensure that the rice noodles or pasta ensure complete submersion and uniform heating throughout the cooking process. They will be boiled for 10 min, after which the excess water will be drained thoroughly before being incorporated in the test diet. The time of the first bite will be synchronized with the glucose monitor intervals and recorded for each participant. The participants will be directed to refrain from consuming any additional food or to avoid engaging in strenuous physical activity for ≥3 h following the consumption of the test diet.

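### The germ-rice row of Table 1 does not fit the stated rice-cooking recipe, so either one of them is misreported or the 175 g portion misses the protocol's own 50 g carbohydrate target

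*Protocol article*

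**What the plan says.** Under Test diets, the staple is the only component that varies between meals, and each staple is to supply 50 g of available carbohydrate. The Table 2 footnote repeats this: "The available carbohydrate content for each staple food was standardized to 50 g". Table 1 gives composition per 100 g in the cooked, ready-to-eat state. In the column order protein, fat, total carbohydrate, fiber, available carbohydrate, its three rice rows read "Refined rice 2.80 0.2 35.4 0.378 35.0", "Brown rice 2.89 1.0 31.7 2.830 28.9" and "Germ rice 2.38 0.5 29.1 0.474 28.6". Table 2 sets cooked portions of 143 g refined, 173 g brown and 175 g germ rice.

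The cooking method is given under Study procedures, after the legend of Figure 1: "The cooking of each staple food follows strictly standardized preset procedures, using a fixed staple-to-water ratio and cooking time". For the three rices it states that "the ratio of staple food (grams) to water (milliliters) is 1:1.25, and they will be cooked for 40 min", in one named rice cooker. Draining is described only for rice noodles and pasta. The article gives no raw-grain moisture, does not mention rinsing or soaking, and does not say what water ratio was used for the analysed batches.

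**The concern.** A cooked weight is a reliable measure of carbohydrate only if the water content at serving equals that at analysis. The recipe gives all three rices the same water per gram of grain, yet Table 1 shows germ rice as much wetter than refined rice.

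If germ rice is served drier than the analysed sample, each 175 g portion carries more carbohydrate than intended. The excess would recur for every participant in all three periods, so neither randomized order nor replication would remove it, and analysts blinded to the food codes could not see it. A portion effect would then be read as a food effect in each germ-rice contrast judged against the 0.78 mmol/L MCID, at individual and population level. Equation 2 scores each food against the other four, so germ-rice contrasts enter the weighted glycemic response score (WGRS) of all five foods.

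**Working it through.** **Inputs.** Tables 1 and 2 (Test diets) and the 1:1.25 ratio (Study procedures), taken as grams of raw rice to mL of water. Raw-grain moisture *m* is not in the documents and is assumed at 12–18%. Ash is not in Table 1 and is tried at 0 and 1 g/100 g.

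**1. Reproduce Table 2.** Portion = 50 / (available carbohydrate per 100 g) × 100.
- Refined: 50/0.350 = 142.9 g (stated 143)
- Brown: 50/0.289 = 173.0 g (173)
- Germ: 50/0.286 = 174.8 g (175)
- Rice noodles: 50/0.253 = 197.6 g (198)
- Pasta: 50/0.281 = 177.9 g (178)

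All five agree, so the portions come straight from Table 1.

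**2. Upper limit on cooked yield.** 1 g rice + 1.25 g water = 2.25 g cooked per g raw at most. Evaporation lowers this.

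**3. Raw moisture that Table 1 would require.** Solids S = protein + fat + total carbohydrate (fiber is already inside total carbohydrate: for germ rice 29.1 − 0.474 = 28.6). Required *m* = 1 − 2.25 × S/100.

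| Rice | S, g/100 g | 2.25 × S | Required *m* | With 1 g ash |
|---|---|---|---|---|
| Refined | 2.80 + 0.2 + 35.4 = 38.40 | 86.4 | 13.6% | 11.4% |
| Brown | 2.89 + 1.0 + 31.7 = 35.59 | 80.1 | 19.9% | 17.7% |
| Germ | 2.38 + 0.5 + 29.1 = 31.98 | 72.0 | 28.0% | 25.8% |

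If 10% of the water evaporates, the yield is 1 + 1.125 = 2.125 and germ rice would need 1 − 2.125 × 0.3198 = 32.0%.

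**4. Comparison that assumes no moisture value.** At any common yield, raw dry matter is proportional to cooked solids: (1 − m_germ)/(1 − m_refined) = 31.98/38.40 = 0.833, so germ rice is 38.40/31.98 = 1.20 times more dilute. If refined rice held no water at all, raw germ rice would need 16.7% moisture; with refined rice at 10%, germ rice would need 1 − 0.833 × 0.90 = 25%. Protein per g of carbohydrate is nearly the same in the two rows (2.80/35.4 = 0.079; 2.38/29.1 = 0.082), which looks like similar grain cooked with more water.

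**5. Carbohydrate delivered if cooked at 1:1.25 without evaporation.** Delivered = portion × (available carbohydrate/100) × [(1 − m)/2.25] / (S/100).

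| Portion | *m* = 12% | *m* = 14% | *m* = 18% |
|---|---|---|---|
| Germ, 175 g | 61.2 g | 59.8 g | 57.0 g |
| Brown, 173 g | 54.9 g | 53.7 g | 51.2 g |
| Refined, 143 g | 51.0 g | 49.8 g | 47.5 g |

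Example, germ at 14%: 175 × 0.286 = 50.05; (0.86/2.25)/0.3198 = 1.195; product 59.8 g. At 18% with 1 g ash: 50.05 × (0.82/2.25)/0.3298 = 55.3 g.

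**6. Water ratio that Table 1 implies.** At *m* = 14%, the germ-rice yield is 0.86/0.3198 = 2.69, i.e. about 1:1.69 rather than 1:1.25 (1:1.56 at *m* = 18%).

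**The case against.** The strongest reply is that the portions may be right. The Beijing Institute of Nutritional Resources analysed the cooked foods, and its restaurant prepares the meals under fixed procedures. If one kitchen procedure served both purposes, 175 g carries 50 g whatever ratio the article prints, and the fault is only in the reporting of the recipe. This stands. A reader might infer that unequal carbohydrate is established, but nothing in the article says that the analysed batch was cooked differently from the meals.

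Second, rinsing or soaking could add water that the ratio does not count, and an article may leave such kitchen detail to the full protocol. The refined row also fits only if almost nothing evaporates: at 10% loss it would need 1 − 2.125 × 0.384 = 18.4% moisture. So the conflict is not a strict impossibility. Equal extra water does not resolve it, however. At 13.6% raw moisture germ rice needs a yield of 86.4/31.98 = 2.70, and at that yield refined rice would hold 38.40 × 2.70 = 103.7 g solids per 100 g raw grain. The rices would have to take up or lose water to clearly different degrees, which the article does not describe.

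Two further inferences are tempting and unsupported. One is that the rice-noodle and pasta rows were swapped, because rice noodles show 18.3 g protein per 100 g carbohydrate against 7.9–9.1 in the rices. Pasta, at 3.69/29.6 = 12.5, is also above the rices, so a swap would not give a rice-like row, and neither product is specified. The other is a bias expressed in mmol/L: the article gives no relation between carbohydrate load and glucose peak. The staple is also not the meal's only carbohydrate source (milk and tomato are served too), so a 20% excess in the staple is less than 20% of the meal.

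**Conclusion.** The conflict between Table 1 and the recipe holds for germ rice. It persists for any raw moisture below about 26% if no uncounted water is added, and evaporation widens it. Brown rice shows a weaker form (18–20% moisture needed), and refined rice is just consistent.

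The consequence is conditional. Either the recipe or the germ-rice row is misreported, or the portions miss the 50 g target. In the last case germ rice would carry about 57–61 g (about 55 g at the lenient end, 18% moisture with 1 g ash) against about 50 g for refined rice, and every germ-rice contrast and WGRS would be biased. These figures assume raw moisture of 12–18%, no evaporation and no rinse or soak water. The documents do not settle which alternative applies. Because equal carbohydrate underlies every food comparison and an excess fixed per food cannot be separated from the food effect afterwards, the point should be settled before meals are served.

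**What to change.** - **Before the first test day**, reconcile Test diets with Study procedures. Confirm from laboratory and kitchen records the water ratio, any rinsing or soaking, and the cooked-to-dry yield of the analysed germ and brown rice batches.
- Correct whichever section is wrong, and recalculate Table 2 if the Table 1 values change.
- Weigh each cooked batch, compute its yield, and use it to check that the portion meets the stated 50 g target.
- **If meals have already been served**, report the carbohydrate actually delivered per food and limit the germ-rice conclusions accordingly. Adjusting for delivered carbohydrate will not rescue the comparison: a covariate that is constant within a food is aliased with the food term in Equation 1.

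The cost is one check of records, at most a repeat analysis of a cooked batch at the same institute, plus weighing each batch.

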### Randomization

The randomization process for the trial will be conducted by a statistician who is not involved in the data analysis to ensure impartiality. Allocation concealment will be achieved using sequentially numbered, opaque, sealed envelopes. The test diets will be designed in alphabetical letters. A random sequence will be generated using R software (R Foundation), with each participant’s order being independently randomized for each period. The order will be provided directly to the food preparation staff, who have no involvement in data collection and analysis. This study strictly implemented analyst blinding. Specifically, the statisticians responsible for data analysis remained completely unaware of which specific staple foods the letter codes represented until the final analysis was completed, and the results were locked.

### Sample collection

Following enrollment, participants will be required to provide fasting blood and stool samples during the run-in period to facilitate subsequent biochemical analyses. The collected biological samples will be stored at −80 °C. Fasting blood will be used to test for lipids (total cholesterol, triglycerides, HDL cholesterol, LDL cholesterol, hemoglobin A1c, fasting blood glucose, serum antiglutamic acid decarboxylase antibodies), as well as liver and kidney health markers. Metagenomic sequencing technology will be used to analyze the gut microbiota, providing information on the microbial abundance at various taxonomic levels (phylum, class, order, family, genus, and species) for each sample. Fecal sample DNA will be extracted using the MagPure Stool DNA KF Kit B (Magen Biotech), strictly following the manufacturer’s instructions. Subsequently, metagenomic sequencing of the participants’ fecal DNA samples will be performed using the Illumina HiSeq X sequencing platform (Illumina Inc). The data will undergo quality control using Fastp (v0.20.1) software. Kraken2 will be used for the taxonomic classification of all valid sequences across the samples. MetaGeneMark will be used for gene prediction from the assembled sequences, and the predicted genes will be annotated using commonly used functional databases.

